| Project Protocol |
| --- |
| Principal Investigator Associate [name] |
| Project name  Does weekly iron supplementation increase iron uptake in pregnant women and improve maternal and infant health? |
| **Lay Abstract** |
|  |

Anaemia and its main cause, iron deficiency, are common in pregnant women in developing countries and adversely affect infant and child health. As well as increasing maternal mortality, maternal iron deficiency anaemia is associated with premature birth, and low birth weight, which in turn is associated with childhood stunting. Children born to iron deficient mothers are more likely to be iron deficient, with increased risks for impaired intellectual development and poorer school outcomes in adolescence. Recently, small studies suggest that iron deficiency in a mother may also increase rates of postpartum depression, which may lead to reduced maternal cognitive functioning and sensitivity and responsiveness to her baby. The infants of depressed mothers in these settings are more likely to be stunted and underweight and to have diarrhoeal diseases and less likely to be completely immunized than infants whose mothers are not depressed. Daily iron, together with folic acid, is recommended by the World Health Organization for pregnant women but often not taken because of unpleasant side-effects, or variable availability. Better strategies are needed to maintain iron stores and decrease anaemia rates during pregnancy to ensure the best health outcomes for mothers and their infants.

Current guidelines in Vietnam recommend iron-folic acid supplementation in pregnancy taken daily. However supply of tablets is variable and compliance is poor and up to 60% of women become anaemic during pregnancy. Weekly iron-folic acid supplementation for pregnant women is a possible alternative to daily supplements and has been shown to be effective in small research studies. Multiple micronutrient supplements (MMN), which contain iron and other micronutrients, are another option for use in pregnancy. A recent study in China showed that MMN given daily in pregnancy resulted in increased infant birth weight, but a slightly higher rate of prematurity when compared to daily iron-folic acid supplementation.

We have shown in a large population-based program that weekly iron-folic acid supplementation reduces anaemia rates in non-pregnant Vietnamese women by 52% over 12 months. A weekly regime of iron-folic acid or MMN supplementation started in adolescence and continued throughout the reproductive years, including in pregnancy, may result in better compliance by women, fewer side-effects and an easier administrative system, leading to increased availability of supplements to pregnant women. However, more information is needed about the use of intermittent supplementation in pregnancy with both iron-folic acid and MMN.

In this study, we will compare the effects of three different methods of iron supplementation in 1224 pregnant Vietnamese women on maternal haemoglobin and iron stores, infant birth weight, and infant anaemia, infant height, weight and developmental screening during the first 12 months of life. Maternal depression will be correlated with infant growth and development, after controlling for maternal iron status. Prior to the study we will consult widely with provincial health officials, community leaders, health workers and community members to ensure high levels of community participation in the project. All pregnant women who are <20 weeks gestation during the recruitment period will be invited to participate and will be assigned to one of three study arms depending on the commune they live in. Women will take either (i) two capsules of iron-folic acid per week (60 mg elemental iron/capsule), or (ii) one capsule of iron-folic acid per day (60mg iron/capsule), or (iii) two capsules of MMN per week (60mg iron/capsule). Women will have their height and weight measured at the third trimester, and at 6 months postpartum, as well as having blood tests to measure haemoglobin, iron stores and other micronutrients. Infant birth details will be recorded, and infant growth and development will be assessed at 6 months after birth. Infants will be checked for anaemia and iron deficiency at 6 months.

Vietnam is currently considering a nationwide weekly iron-folic acid (or MMN) supplementation program for non-pregnant women of reproductive age. Our results will clarify whether this is also the best approach for use when women become pregnant. If so, women could use weekly iron supplementation throughout their reproductive years, including during pregnancy. The practical outcome will be new information about the clinical impact of different iron supplementation approaches on maternal and infant health. More broadly this research has the potential to vastly increase compliance with and improve the distribution of iron supplements in pregnancy, which will lead to improved effectiveness with reduced rates of iron deficiency and anaemia, increased birth weight, and improved infant growth and development and in the long term school performance.

| Principal Investigator Associate [name] |
| --- |
| **Scientific Abstract** |
|  |

Iron deficiency anaemia is widely prevalent in pregnant women despite global and national policies for daily iron supplementation in most countries. This is because of variable availability of supplements at the primary level, and poor compliance due to unpleasant side-effects. Maternal iron deficiency has serious repercussions for maternal and infant health, and is linked with increased risk of maternal death, preterm delivery, intrauterine growth retardation, low birth weight, and impaired infant growth and development. Preliminary evidence suggests that iron deficiency may also be a cause of maternal depression in the perinatal period, which may impact adversely on fetal growth and infant development in the early years. WHO advocate iron and folic acid supplementation taken once a week for non-pregnant women living in areas with high rates of anaemia. We have demonstrated that a population-based weekly iron folic-acid supplementation program for non-pregnant women in North Vietnam reduced anaemia rates by 50% over a 30-month period [1, 2]. Small studies have shown that weekly supplements are also effective in maintaining haemoglobin (Hb) in pregnancy, and emerging evidence suggests that small daily doses of iron during pregnancy, as well as weekly or intermittent dosing starting early in pregnancy, are safer and essentially as efficacious as daily iron in preventing iron deficiency and improving iron stores. Multiple micronutrient supplements (MMN), which contain iron and other micronutrients, are another option for use in pregnancy. A recent study in China showed that MMN given daily in pregnancy resulted in increased infant birth weight, but a slightly higher rate of prematurity when compared to daily iron-folic acid supplementation [3]. A weekly regime of iron-folic acid or MMN supplementation started in adolescence and continued throughout the reproductive years, including in pregnancy, may result in better compliance by women, fewer side-effects and an easier distribution system, leading to increased availability of supplements. However, it remains to be determined if weekly iron-folic acid or MMN supplements will be as effective as the recommended daily iron-folic acid when given in a large randomized controlled trial in a resource-constrained country, and whether there will be measurable benefits in maternal haemoglobin and iron stores, birth outcomes and infant growth and development. The Vietnamese Government acknowledges maternal and infant nutrition, and childhood stunting as urgent priorities.

Research Plan

We will conduct a cluster-randomized controlled trial in Hanam province, where there were 11,551 recorded births in 2008. We will randomize 102 communes to one of the three intervention arms of the study, and all women that are pregnant during the recruitment period and less than 16 weeks gestation will be invited to participate. We will recruit 1224 pregnant women who will take either (i) two capsules of iron-folic acid per week (60 mg elemental iron/capsule), or (ii) one capsule of iron-folic acid per day (60mg iron/capsule), or (iii) two capsules of MMN per week (60mg iron/capsule).

Aims 1. To compare the effect of twice weekly provision of iron-folic acid or MMN supplements, with the recommended daily iron-folic acid supplements during pregnancy on maternal and infant outcomes (including the primary outcome of birth weight; and secondary outcomes of maternal haemoglobin and ferritin at 32 weeks, and infant height for age z scores, haemoglobin, ferritin and cognitive developmental scores at 6 months of age).

2. To compare the effect of twice-weekly provision of iron-folic acid supplements with twice weekly MMN during pregnancy on maternal and infant outcomes, using similar outcomes to Aim 1.

Outcomes and Significance: Vietnam is currently considering a nationwide weekly iron-folic acid or MMN supplementation program for non-pregnant women of reproductive age. Evidence from this study will clarify whether this approach is also suitable for use when women become pregnant. This would increase availability of supplements by allowing easier distribution at village level, and would likely reduce side effects compared to the currently recommended (although poorly administered) daily provision of iron-folic acid supplementation. It will extend previous studies by measuring clinical outcomes of different iron supplementation approaches and the impact on infant outcomes.

| Principal Investigator Associate [name] |
| --- |
|  |
|  |
| Specific Aim(s) of the Project |

**Specific Aims**

1. To compare the effect of twice weekly provision of iron-folic acid or MMN supplements, with the recommended daily provision of iron-folic acid supplements during pregnancy on maternal and infant outcomes during pregnancy and the first 6 months of life (including the primary outcome of birth weight; and secondary outcomes of maternal haemoglobin and ferritin at 32 weeks, and infant height for age z scores, haemoglobin, ferritin and cognitive developmental scores at 6 months of age).

2. To compare the effect of twice weekly provision of iron-folic acid supplements with twice weekly MMN during pregnancy on maternal and infant outcomes during pregnancy and the first six months of life, using similar outcomes to Aim 1.

| Principal Investigator: Associate [name] |
| --- |
| Background and Significance |

Maternal and child health are major health priorities in countries in the Western Pacific region and globally [4]. Under-nutrition is the cause of 3.5 million child deaths/year and it is estimated that at least 200 million children in less developed countries are prevented from attaining their optimal developmental potential due to poverty and associated health, nutrition, and psychosocial factors [5]. Four key risk factors have been identified as main contributors to this situation, stunting, inadequate cognitive stimulation, iodine deficiency, and iron deficiency anaemia, and there is an urgent need to address them. Overall infant physical and mental development is increasingly impaired as these risks accumulate [5], [6], [7] . Maternal iron deficiency anaemia is an important contributor to these risk factors and will be addressed in our study.

Stunting, the most definitive indicator of chronic, rather than acute, under-nutrition, may affect the development of a child from the early stages of conception through to the third or fourth year of life [8], [9]. It is due to a combination of maternal factors causing inadequate foetal growth before birth; and postnatal factors such as extended periods of inadequate food intake, poor dietary quality, or significant illness [5]. Maternal iron deficiency increases risks of intrauterine growth retardation and low birth weight [10], which are associated with stunting. Infants who experience iron deficiency during the first 6-12 months of life are likely to experience developmental delays in cognitive, social-affective and motor performance that may persist for years, [11], [12], [13], [14]. Maternal anaemia has been shown to be a predictor of iron deficiency in infants [15], [16]. WHO estimate that 42% of pregnant women and 47% of preschool children globally have anaemia, of which 60% is likely to be due to iron deficiency [17]. As well as leading to a reduction in physical and mental capacity, iron deficiency is linked with increased risk of maternal death, preterm delivery, low birth weight, increased neonatal mortality and impaired infant development [18], [19], [16]. Dietary deficiency of bioavailable iron and increased iron demands during pregnancy, blood loss from menstruation and other causes such as intestinal hookworm infection are major contributors to iron deficiency in women in less developed countries [18]. Many women become pregnant with insufficient iron stores to ensure optimal foetal growth and development and satisfactory pregnancy outcomes [20].

In Viet Nam a daily iron supplementation program for pregnant women has been in operation since in 1993 [28]. The failure of daily iron programs to significantly reduce maternal anaemia is due to limited or variable availability of supplements and poor compliance because of unpleasant gastrointestinal side-effects [28]. Therefore, better strategies are needed to maintain iron stores and decrease anaemia rates during pregnancy to ensure the best health outcomes for mothers and their infants. Weekly provision of iron supplementation for pregnant women may be an effective strategy for overcoming compliance issues related to daily supplementation. [29], [30]. This approach has the advantage of few side-effects and easy distribution at community level, and emerging evidence suggests that small daily doses of iron in pregnancy, as well as intermittent dosing starting early in pregnancy, are safer and essentially as efficacious as daily iron in preventing iron deficiency and improving iron stores[20]. Involving village health workers in encouraging iron supplementation during pregnancy was shown to be effective in reducing anaemia rates in Thailand [31], and in Vietnam involvement of village health workers in iron distribution may overcome the difficulties that rural women have in accessing appropriate supplementation during pregnancy. Recent evidence also suggests that MMN supplements may be desirable in pregnancy, leading to increased birth weights compared to iron-folic acid [3] , [32].

In this context, Australian and Vietnamese researchers have formed a partnership to conduct this study among pregnant women in Hanam province, Viet Nam, to investigate the most effective form of iron supplementation during pregnancy on functional maternal and infant outcomes. The research will extend previous studies by measuring clinical outcomes of different iron supplementation approaches on infant health.

A demonstrated effective strategy for improved uptake of antenatal iron supplementation with significant improvements in infant growth and development would have broad implications for policy development in Vietnam and resource-constrained countries in the region. The research, to be conducted in collaboration with WHO, has the potential to rapidly change policy and practices if intermittent iron-folic acid or MMN are shown to be superior, leading to increased compliance, availability and effectiveness of iron supplementation in pregnancy, reduced rates of iron deficiency and anaemia, and improved birth weight, infant growth and development and in the longer term, school performance.

| Principal Investigator Associate [name] |
| --- |
| Supportive Preliminary Data |

Viet Nam initiated a daily iron supplementation program for pregnant women in 1993 [28]. We have recently shown that weekly iron-folic acid supplementation and deworming is a practical and effective way to reduce anaemia and hookworm prevalence in women of reproductive age (Fig 1) [35], [2].

Figure 1. Change in mean Hb for non-pregnant anaemic and non-anaemic women sampled at baseline, three and 12 months after commencement of a weekly iron-folate intervention and deworming. The prevalence of anaemia fell from 37.5% [CI 30.9, 44.1]) to 19.5% [CI 15.4, 23.7]), and of hookworm infection from 76.2% (CI 68.2-82.8) to 25.2% (CI 20.6-30.1, P<0.001) over the one year study period, [1], [2].

In those who became pregnant during this study, increased birth weight was observed in the group with access to the weekly iron-folic acid supplementation program compared to controls.

Table 1. Mean birth weight, % low birth weight in neonates of women who became pregnant in districts where a weekly iron-folic acid and deworming program had been operational, compared to those in control districts.

|  | Mean Birth Weight | Low birth weight |
| --- | --- | --- |
| Intervention districts (N 168) | 3135g (95% CI 3080-3190) | 2.9% |
| Control districts (N 295) | 3011g (CI 2960-3062) | 7.1% |
| Difference | +124g (CI 49-199) | -4.2%  RR 0.42 (CI 0.16-1.09) |
| P Value | 0.001 | 0.045 |

In a recent survey in Yen Bai, many women kept taking weekly iron-folic acid supplements during pregnancy if they could not get access to daily supplements through antenatal clinics or privately.

As a result of these findings, we have worked with the Government of Vietnam and WHO to reach all 250,000 non-pregnant women of reproductive age in Yen Bai with weekly iron-folic acid supplementation [35]. One of the key factors in this program has been implementation at village level with community engagement and health services strengthening through education and training of all village health workers in the province, and improved linkages between commune and village level [35]. We are currently participating in the development of a ‘Plan of Action to Accelerate the Reduction of Child Stunting in Viet Nam’ [33], which includes weekly iron for non-pregnant women on a national scale. The proposed study will build on this initiative by determining if intermittent iron-folic acid or MMN is a more effective approach for iron supplementation for pregnant women when compared to daily supplementation in reducing anaemia, and improving iron status, birth weight and infant growth and development. If successful, this evidence would support continuation of weekly iron-folic acid supplementation in women throughout their reproductive years, starting in adolescence taking 60mg elemental iron once a week and increasing to 120mg iron a week during each pregnancy.

| Principal Investigator Associate [name] |
| --- |
| **Experimental Design and Methodology** |
|  |

**Setting**

Although considerable progress in health indicators has been made in Vietnam in the last decade, there is still a high prevalence of chronic malnutrition and stunting among the under five population and of low birth weight; relatively high maternal and neonatal mortality, mainly in ethnic minorities and in remote areas, and an increasing prevalence of life-style related diseases (including suicide, and mental health disorders). Maternal and infant mortality rates among ethnic groups are much higher than the national averages, social inequalities have increased and infant mortality in the poorest 20% is increasing [40] .

We will undertake this project in Hanam Province, Viet Nam, which has a population of approximately 820,100 people, with most still living in rural areas and working in subsistence agriculture. The main town is approximately 60 km from Hanoi. There are six districts and 116 communes. The province is relatively small and has a high population density (845.8km2 and 968 people/km2) [41] so travel time between communes is quite short. At least 80% of births take place in commune health centers with most others occurring in district hospitals. We chose Hanam province for this project because of its closer proximity to Hanoi, which will make the project easier to implement. Within Vietnam, the project will be hosted by the Research and Training Centre for Community Development (RTCCD), a Vietnamese NGO, who will oversee project implementation in Hanam province and will liaise and collaborate with national and provincial Vietnamese Government authorities, including the National Institute for Nutrition, the National Institute for Malariology, Parasitology and Entomology, the Provincial Health Department and the Provincial Maternal and Child Health Service. An Australian project officer will be located in Vietnam to oversee the project.

**Approach and Methodology**

Design: We propose to conduct a cluster-randomised controlled trial of iron supplementation in pregnant women commenced before 16 weeks gestation. A placebo-controlled trial was not contemplated as we considered it unethical to withhold iron supplementation during pregnancy. The trial will have three intervention arms as follows: (1) one capsule of iron-folic acid (IFA) to be taken twice a week (60mg elemental iron /capsule, 2 capsules per week), or (2) one IFA tablet to be taken daily (60mg elemental iron /tablet; 7 tablets per week), or (3) one capsule of MMN to be taken twice a week (60 mg elemental iron/capsule, 2 capsules per week).

Supplements: We have chosen a local pharmaceutical manufacturer, Nam Ha Pharmaceutical Company, to produce the IFA and MMN supplements for the clinical trial. This company has produced IFA supplements for our Yen Bai WIFS program for the last 4 years and has WHO GMP certification. The supplements will require limited registration by the Ministry of Health for use for research purposes.

The formulation of the three types of supplements is shown in the table below.

**Formulation of Supplements -Amount in each capsule**

| Content | Weekly Iron-folic acid1 | Weekly multi-micronutrients 2 | Daily iron-folic acid3 |
| --- | --- | --- | --- |
| Elemental Iron | 60mg | 60mg | 60mg |
| Zinc |  | 20mg |  |
| Iodine |  | 300µg |  |
| Copper |  | 4mg |  |
| Selenium |  | 130µg |  |
| Vitamin A |  | 1.6mg |  |
| Vitamin B |  |  |  |
| - B1 (thiamine) |  | 2.8mg |  |
| - B2 (riboflavin) |  | 2.8mg |  |
| - niacin |  | 36mg |  |
| - B6 |  | 3.8mg |  |
| - B12 |  | 5.2µg |  |
| - Folic acid | 1.5mg | 1.5mg | 0.4mg |
| Vitamin C |  | 140mg |  |
| Vitamin D |  | 400IU |  |
| Vitamin E |  | 20mg |  |

1. Two capsules to be given each week = 120mg iron, 3mg folic acid/week. These will be identical to the MMN tablets.

2. Two capsules to be given each week = 120mg iron, 3mg folic acid, 40mg zinc + approx 4xRDI of other micronutrients.

3. Seven tablets to be given each week = 420mg iron, 2.8mg folic acid

The MMN will contain similar micronutrients to the UNICEF-recommended UNIMMAP daily supplement [43], except that we will include 2x the amount of micronutrient in each capsule (as women will only take two capsules a week). This means that women will receive 4/7 of the amount of micronutrients per week that they would have received from a daily UNIMMAPP supplement. The exception to this is folic acid. Each of the supplements will contain 1.5mg of folic acid.

Treatment allocation and recruitment: The study will be undertaken in 5 districts of Hanam Province (and will exclude the main provincial town). The commune was chosen as the cluster unit of randomization to reduce the likelihood of interactions between the intervention groups. Communes agreeing to participate in the study will be randomly assigned to one of the three treatment arms: twice weekly provision of IFA, daily provision of IFA, or twice weekly provision of MMN. Randomization will be performed by an independent statistician using ‘ralloc’ in the statistical program Stata (StataCorp, College Station, TX, USA).

Lists kept at commune level will be used to identify all pregnant women in selected communes and all eligible women will be invited to participate by the research team, in conjunction with local village and commune health workers. In Hanam province we expect approximately 1990 live births per district/year (personal communication PI 4). All women in the trial communes that are <16 weeks gestation during the recruitment period will be considered for inclusion in the study. Women with complicated pregnancies (e.g. twins, diabetes, other medical conditions), or Hb<80 g/L will be excluded from the study and referred for medical treatment.

We expect recruitment to take approximately 8 weeks. However, a flexible approach will be taken and the research team will work closely with provincial counterparts to determine the best strategies for recruitment, which may involve recruiting over a longer time period. We plan to increase the recruitment of women in the first trimester of pregnancy by using village and commune health worker staff to inform women who are recently married or trying to become pregnant about the study, and to encourage them to come for early pregnancy testing. In this way we hope to recruit women from six weeks gestation. Written informed consent will be obtained at enrolment.

Reducing bias by blinding the researchers and participants to the intervention, and by training: The two arms of the trial with intermittent supplementation will be blinded. The supplements will be produced by Nam Ha Pharmaceutical Company, Vietnam, who will undertake the blinding process. The IFA and MMN capsules that will be taken twice a week will be identical and a code will be embossed on each blister pack, with the code known only to the manufacturer and the chairperson of the Data Monitoring and Safety Committee.

The daily intervention cannot be blinded to the participants or the field team. To try to overcome biases we plan to promote the project to participants and commune staff as a study of different supplements for use in pregnancy without explicitly informing participants about the schedule in other arms of the study, in this way minimizing the chance of women believing they are not getting ‘enough’, or getting ‘too much’, iron. We will also make it clear that the optimal amount of iron for use in pregnancy is still in doubt. Training sessions for researchers and health workers will emphasize the importance of being objective in all aspects of the study. We do not expect bias in any of the laboratory measures because the laboratory staff will be unaware of the intervention groups.

We will train the research team and selected commune and hospital staff to make triplicate measurements (e.g. birth weight, maternal and infant anthropometry) and select the middle measurement. A second observer will check the measurements. RTCCD staff will administer the depression scales and will not be blinded to the daily intervention. However these are experienced research staff using standard structured tools and with appropriate training we hope to limit bias in the interviews.

Distribution of the supplements and monitoring: At enrolment, women will receive blister packs containing two month’s supply of intervention. A senior RTCCD project officer and a local provincial project officer will be assigned to each arm of the study for monitoring visits and the senior person will provide ongoing training and supervision to the local staff member through out the project. Each woman will be visited approximately every six weeks to distribute the intervention for the next period. At this visit, the researcher will collect old blister packs and record the number of tablets consumed, as well as seeking information about compliance, side effects and pregnancy complications. Monitors will also encourage women to attend the commune health station for delivery. We expect tracking for follow up to be straightforward because there are relatively low rates of whole household relocation in Vietnam. Retention rates using these strategies have previously been high [42].

Exclusions and loss to follow-up: A recent observational study in Ha Nam recruited 500 pregnant women of whom none were severely anaemic (Hb <70g/L) and we anticipate this will be similar in this trial. While we have no quantitative data from Hanam on complicated pregnancies, anecdotal reports from the field suggest these are less than 5% of all births. One likely problem will be drop-outs by women who are reluctant to provide a blood sample at 32 weeks. Data from the observational study suggested that this could be as high as 15%.

Ethics: To protect privacy, code numbers and not names will be used. Other ethical considerations are outlined in the Australian National Ethics Application Form which was recently submitted and approved by the Melbourne Health HREC. Amendments will be sought from the HREC for any significant changes to the protocol that need to be made in the planning phase.

Assessment of women will occur at study enrolment, 32 weeks gestation and 6 months postpartum and of infants at birth and 6 months of age as follows:

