**2. Infants**

| **Measure** | **Birth** | **6 months of age** |
| --- | --- | --- |
| Birth assessment | √ |  |
| Infant anthropometry (wt, length, HC) | √ | √ |
| Developmental Screening using Bayley Scales |  | √ |
| HemaCue test for Hb |  | √ |
| Venipuncture blood sample |  | √ |

Sample size calculations

Hb data from pregnant women in Hanam province on which to base our sample size estimates and data regarding the number of pregnant women available for recruitment has recently been collected in an observational study. There were on average 10 eligible pregnant women of 12 to 20 weeks gestation per commune (mean 10, range 2-20). In the proposed study all eligible pregnant women in communes allocated to each arm of this study will be invited to receive the intervention.

This cluster randomized trial will recruit 34 communes / 408 pregnant women per treatment arm (i.e. a total of 1224 women from 102 communes) where the average commune size is 12 women per commune and it is expected that 5% of women will be excluded due to pregnancy complications and 15% will be lost to follow-up.

With 95% confidence the above sample size has at least 80% statistical power to detect clinically important differences of 6 g/L for haemoglobin (power = 98%, SD=12g/L, ICC=0.12)[[1]](#footnote-2), 100g for birthweight (power = 81%, SD= 389g, ICC=0.03)[[2]](#footnote-3), and 0.3 for the height for age Z-score (power = 93%, SD=0.9, ICC=0.05)[[3]](#footnote-4). The above sample size calculations were performed using ‘sampsi’ and ‘sampclus’ in the statistical program Stata (StataCorp, College Station, TX, USA).

Our primary hypotheses (and sample size estimates) are based on continuous measurements to ensure that all information is included. The optimal Hb in late pregnancy is not clear as there is evidence that moderately low and higher haematocrits may impair birth outcomes. We are also interested in the absolute mean change of ferritin at 32 weeks, as this will reflect the effectiveness of the intervention in maintaining womens’ iron stores into the third trimester of pregnancy. This approach may reduce our power to asses change in percentage of women with anaemia or iron deficiency.

Data Management

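### The commune allocation names no stratification by district and the models carry no district term, so district balance is left to chance; this is an inexpensive improvement, not an error

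*Protocol*

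**What the plan says.** **Allocation.** Treatment allocation and recruitment states "The study will be undertaken in 5 districts of Hanam Province", leaving out the main provincial town. It continues: "Communes agreeing to participate in the study will be randomly assigned to one of the three treatment arms". On method it says "Randomization will be performed by an independent statistician using" the Stata command `ralloc`. It gives neither strata nor block sizes, and it does not say that the list is unstratified.

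**Size.** Sample size calculations states "This cluster randomized trial will recruit 34 communes / 408 pregnant women per treatment arm", 102 communes in all, where "the average commune size is 12 women per commune". For birth weight, the primary outcome, it gives a difference of 100 g, SD 389 g, ICC 0.03 and power 81%.

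**Analysis.** Both Aim 2 and Statistical Analysis describe linear mixed models with a random effect for commune. The baseline value is the only covariate named, and only for haemoglobin and ferritin. District appears in neither place.

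**Where births occur.** Setting says "At least 80% of births take place in commune health centers with most others occurring in district hospitals". Under Standardization of anthropometric measurements, nominated labour-ward staff in the five district hospitals join the measurement training.

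**The concern.** District is a natural stratum here. Communes sit within five districts, and up to about a fifth of births take place outside commune centres, mostly in district hospitals. True birth weight may differ between districts, and so may recorded weight.

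If the list is drawn across all 102 communes at once, the arms will not be evenly spread over districts. With no district term in the model, whatever variation lies between districts is then counted as commune-level noise in the comparison of arms. Planned power for the primary outcome is only just above the 80% target, so a small gain in precision would be useful.

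Strata have to be settled before communes are allocated. Unlike a covariate, they cannot be added later in an analysis plan.

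**Working it through.** **Inputs from Sample size calculations.** 408 women per arm in 34 communes, 12 per commune; 5% excluded and 15% lost; birth weight difference 100 g, SD 389 g, ICC 0.03. A two-sided 5% level is assumed from the stated 95% confidence.

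**Step 1: reproduce the stated power.**
- Evaluable women per arm: 408 × 0.80 = 326.4.
- Design effect: 1 + (12 − 1) × 0.03 = 1.33.
- Standard error of the difference: 389 × √(2 × 1.33 / 326.4) = 35.1 g.
- Power: Φ(100/35.1 − 1.96) = Φ(0.888) = 81.3%, against 81% stated.

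The same method gives 98.7% for haemoglobin (design effect 2.32; stated 98%) and 92.8% for height-for-age (design effect 1.55; stated 93%). The sample size therefore does not rely on stratification.

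**Step 2: what stratifying and fitting district could add.** Let *f* be the share of the between-commune variance that lies between districts. The Protocol gives no value, so *f* is an assumption and is shown over its whole range. If the district share is removed, the design effect becomes (1 − 0.03) + 12 × 0.03 × (1 − *f*).

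| *f* | Design effect | SE (g) | Power |
|---|---|---|---|
| 0 | 1.330 | 35.1 | 81.3% |
| 0.10 | 1.294 | 34.6 | 82.3% |
| 0.25 | 1.240 | 33.9 | 83.9% |
| 0.50 | 1.150 | 32.7 | 86.5% |
| 1 (ceiling) | 0.970 | 30.0 | 91.5% |

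**Step 3: how much chance imbalance matters, in grams.** Assume districts of 20, 20, 20, 21 and 21 communes; the Protocol gives no counts by district. Under unstratified allocation of 34 communes to each arm, the variance of the between-arm birth-weight difference due to district imbalance is

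*f* × 0.03 × 389² × (2/34) × (102/101) × (1 − Σq²),

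where q is each district's share of communes and 1 − Σq² = 0.80. The last three factors multiply to 0.0475. The resulting SD is 4.6 g at *f* = 0.10, 7.3 g at 0.25 and 10.4 g at 0.50. This is part of the 35.1 g standard error, not an addition to it, provided the ICC of 0.03 includes between-district variation.

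**The case against.** The strongest objection is that the Protocol never says the list is unstratified. It names `ralloc`, which the fix below also uses, and gives no options, so a stratified list is compatible with the text. Unstratified randomisation of 34 clusters per arm is also sound in itself, and the stated powers hold without strata. All of this stands, and it is why the point is not an error. What remains is that the text as written neither secures district balance nor uses district in the analysis.

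The measurement argument is also weaker than it first looks. District hospitals handle at most about a fifth of births. Their labour-ward staff receive the same training, measurements are made in triplicate by two observers, and monitors are to keep scales and measurements uniform across sites. This reduces the expected district effect on recorded weight but does not exclude it, and it does not bear on true differences between districts.

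A reader might infer serious imbalance by counting communes. Under the district sizes assumed above, some pair of arms differs by five or more communes in some district in about 86% of unstratified allocations. That figure covers any of three pairs in any of five districts; for one given pair it is about 56%. It counts communes, not grams, and the effect in grams is small and already within the standard error.

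A reader might also expect stratification to be needed so that every district contains all three arms. In about 99.9% of unstratified allocations every district already does.

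**Conclusion.** The point holds as a minor design improvement. The Protocol mentions no stratification by district and specifies models without a district term, so district balance is left to chance and any between-district variation stays in the error term. Nothing stated is wrong, and the comparison of arms is unbiased either way.

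The gain in birth-weight power ranges from nothing to about 5 percentage points for district shares of 0 to 50% of the ICC, with a theoretical ceiling of about 10 points. The documents do not support calling this a known loss of precision, because they contain no between-district variance. The gain also shows in the standard errors only if district is fitted in the model as well as used in the allocation.

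**What to change.** **If communes are not yet allocated:** have the independent statistician generate the `ralloc` list stratified by the five districts, state this and the block sizes under Treatment allocation and recruitment, and add district as a fixed effect to the linear mixed models under Aim 2 and Statistical Analysis.

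**If allocation is done:** record whether the list was stratified, and prespecify district as a fixed effect before any outcome comparison by arm.

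**Cost:** one setting when the list is produced and four degrees of freedom for district against 102 communes. The sample size does not change. If districts turn out not to differ, practically nothing is lost.
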